### Secondary outcomes

The secondary outcomes are:Women’s level of self-efficacy at 34 weeks, assessed with the General Self-Efficacy scale [24]Pregnancy weight gain assessed by gain in weight between recruitment and 34 weeks gestationMaternal diet quality one month after birthBreastfeeding status one month after birth (yes/no)Neonatal whole body bone mineral content (BMC), lean and fat mass within 2 weeks after birth assessed by dual-energy X-ray absorptiometry (DXA).

## Methods/design

The trial procedures are summarised in Fig. 1.

**Fig. 1 Fig1:**
[figure not shown]
Trial summary: Southampton PRegnancy Intervention for the Next Generation (SPRING)

### Study setting

The setting for the trial is the Princess Anne Maternity Hospital, Southampton, UK. Southampton is a relatively deprived city on the south coast of England and is among the 25 % most deprived local authorities within the UK based on the Index of Multiple Deprivation. Princess Anne Hospital is the setting for the majority of births within the city and provides maternity care for 5000 women each year.

### Recruitment at 8–12 weeks

Women are recruited to the study in early pregnancy, and by around 12 weeks if possible, using an approach that has been successful in the MAVIDOS trial of vitamin D supplementation during pregnancy [9]. Posters in general practitioner (GP) surgeries and in the maternity hospital waiting area publicise the study. Each woman booked for her antenatal care at Princess Anne Hospital is sent an information leaflet outlining the study along with the routine letter she receives inviting her to her nuchal translucency or early dating scan. Research nurses approach women who are attending the Princess Anne Hospital for their nuchal translucency or dating scan between 8 and 12 weeks gestation and invite them to discuss the study, having first checked whether they have read the SPRING information leaflet. If women agree to take part, then the nurses check their eligibility for the study and take them through the consent process. An interpreter can be involved if required.

Women who decline to take part in the study are given an information sheet explaining that we are running a sub-study about why women do not take part in research. They are asked whether they would be willing to complete a one-page questionnaire giving details about their age, educational attainment and number of children, and to indicate the reasons why they declined to take part in the study. It is made clear to women that they are under no obligation to complete the questionnaire. They are also asked whether they would be willing to take part in a 30-minute interview with a researcher to further explore their reasons for declining.

### Healthy Conversation Skills support

Healthy Conversation Skills training is underpinned by Bandura’s social cognitive model, which proposes individual self-efficacy as central to the process of the adoption and maintenance of positive health behaviours. Higher self-efficacy is strongly associated with more healthful behaviours [25]. The training aims to enhance health and social care practitioners’ self-efficacy to address a range of lifestyle issues and support patients and clients to change. Empowering individuals to identify solutions and take first steps towards their goals provides mastery experiences which Bandura proposes is one mechanism for raising self-efficacy.

Healthy Conversation Skills support is delivered by trained research nurses. The trial has a team of six part-time research nurses: three who have contact with women in the intervention group and three who have contact with women in the control group. Intervention nurses receive training in Healthy Conversation Skills. These are skills that support behaviour change, thus enabling practitioners to empower women to change their own health behaviours. The training promotes the development of practitioner skills in reflecting, listening and asking ‘open discovery questions’: those that generally begin with ‘what’ or ‘how’. These questions, when used in conversation, allow a client to explore an issue, identify barriers, generate solutions and set goals. Skills in Specific, Measurable, Action-oriented, Realistic, Timed, Evaluated, Reviewed (SMARTER) goal setting are also developed during the training to enable practitioners and clients to review progress towards meeting goals at each successive meeting. As such, Healthy Conversation Skills training has been developed to incorporate the use of a range of behaviour change techniques (BCTs) [26]. These are used throughout the training sessions, and trainees are introduced to many of them explicitly in some of the training activities. The training programme is described in more detail in Table 1. Control group nurses are trained in study procedures but do not have any specific training in skills to support behaviour change and so do not use open discovery questions or support women to set goals.

**Table 1 Tab1:** Healthy Conversation Skills (HCS) training description

Communication is enhanced through practitioners developing the skill of asking open-ended questions, known as Open Discovery Questions: those that generally begin with ’how’ and ’what’. Such Healthy Conversations allow a patient or client to explore an issue, identify barriers and generate solutions that can be reviewed with the practitioner. Training aims to increase self-efficacy and a sense of control of both practitioners and their patients and clients.
The five core skills are:
1. To be able to identify and create opportunities to hold Healthy Conversations
2. To use Open Discovery Questions to support someone to explore issues, barriers and priorities; problem-solve; generate solutions; and set goals for change
3. To reflect on practice and conversations
4. To spend more time listening than giving information or making suggestions
5. To support someone to make a SMARTER (Specific, Measurable, Action-oriented, Realistic, Timed, Evaluated, Reviewed) plan.
Healthy Conversation Skills training generally consists of two 3–4 hour group sessions over a week or so to allow time for practising and reflecting on skills between sessions. Training is delivered by an HCS trainer experienced in group work and behaviour change to a group of about 8 to 15 trainees. This can be followed by a period of ongoing support, which might include a phone call or face-to-face visit from one of the trainers to find out how skills are being implemented in practice. The phone call and visit allow trainees to reflect on the training, how they have implemented new skills, any barriers to their implementation and plans for continued or increased use, including embedding self and peer reflection as part of normal practice. Both follow-up activities are also opportunities to collect evaluation data to assess the effectiveness of the training in changing staff practice, using customised tools developed by the HCS team.

Once HCS nurses are trained, they are supported to embed the skills rapidly into their practice. Ongoing support is provided by the HCS trainers, who are members of the research team, during regular meetings. Every interaction between nurses and participants is recorded in a Case Report Form, and a sample of appointments for each nurse are audio-recorded and assessed in detail as part of the process evaluation. This approach will allow us to capture variations between nurses.

The objective of having a Healthy Conversation is to explore the woman’s world and support her to identify issues, solutions and goals. She is therefore supported by the trained research nurses to review these topics at each visit. Progress with any previously set goals is explored, and if women wish to change or set new/additional goals, this is entirely acceptable and is recorded by the nurses. A Case Report Form is completed for every participant by each nurse at each visit to record all goals set and the women’s experiences in working towards and achieving these goals, as well as any barriers and unsuccessful attempts to change. The women can set as many or as few goals as they wish.

During the trial, the group of women randomised to receive the behaviour change intervention will meet with a nurse trained in Healthy Conversation Skills on four occasions during pregnancy and once after birth. The control group will have the same number of contacts.

### Vitamin D supplementation

Vitamin D supplementation consists of a daily oral supplement of 1000 IU cholecalciferol. Each woman receives a single box of blister-packed capsules of vitamin D or placebo to last for the duration of her pregnancy. Each pack is individually prescribed for each participant. The trial’s pharmacist allocates a pack to that prescription, documenting both the pack number and the SPRING participant’s unique ID number. These are checked again by the research nurse, who collects them from pharmacy ready to issue to participants at the 14 week visit, and documented in the participant’s notes. The medication comes with a tear-off adhesive label which is placed in the notes as an added safeguard against error in pack allocation. A sticker is applied to the obstetric notes of women taking part in the trial in order to alert clinicians to their enrolment. An information sheet and copy of the consent form are filed in each woman’s notes. The mother (with a copy to the father) is given contact details for the study co-ordinator and research nurse and asked to inform them immediately when labour begins.

The Investigational Medicinal Product (IMP) and matched placebo are manufactured by Sharp Clinical Services (UK) Ltd, [name]. The manufacturer has no role in the trial other than supply of the randomised IMP. As with the MAVIDOS trial, the IMP capsules contain 1000 international units (IU) of cholecalciferol (vitamin D3, supplied by Merck KGaA, Darmstadt, Germany, who also had no other role in the trial), with excipients matched to the placebo capsule [9]. Study medication (active/placebo) is supplied to the local pharmacy pre-randomised 1:1 by the manufacturer, using a computer system, and sequentially numbered for storage and dispensing. Code-break envelopes are supplied to the lead pharmacist but are not available to the investigative team. Emergency code-break access is available through the principal investigator and on-call pharmacist.

### Randomisation

Consistent with the trial’s factorial design, women are randomised to receive Healthy Conversation Skills support or to usual care and to receive a vitamin D supplement or a matched placebo. The impartial trial data manager uses block randomisation to allocate participants to receive support from a practitioner trained in Healthy Conversation Skills, or to usual care. Blocks of 4 are used, each with two 0’s and two 1’s. This ensures that for each 4 participants randomised there will be equal distribution of intervention and control participants. While is it not possible to blind staff to the allocation ﻿of Healthy Conversation Skills, the women themselves will not be told what the intervention entails and so will be blind to the intervention they are receiving. The IMP is pre-randomised by the manufacturer using a computer system. The women are blind to their vitamin D allocation, as are the research team.

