### Study design

The study is a randomised controlled trial that uses a two-by-two factorial design. The two interventions being tested are exposure to nurses trained in skills to support behaviour change (Healthy Conversation Skills) and daily oral vitamin D supplementation (1000 IU cholecalciferol daily). The women taking part in the study and the research nurses delivering the intervention are blind to the vitamin D intervention, so this part of the trial is double blind. However, the same is not possible for the behaviour change intervention. There are four groups of study participants:Healthy Conversation Skills support plus vitamin D supplementationHealthy Conversation Skills support plus placeboUsual care plus vitamin D supplementationUsual care plus placebo.

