### Trial status

The SPRING trial is ongoing.

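### Fixed blocks of 4 for HCS, to which staff are not blind, make up to one third of allocations foreseeable if recruiting staff can follow past allocations in order

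*Protocol article*

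**What the plan says.** The protocol article, under Randomisation, has the trial data manager, described as impartial, allocate women to HCS or usual care. The rule is explicit: "Blocks of 4 are used, each with two 0’s and two 1’s", and its stated purpose is exact balance: "This ensures that for each 4 participants randomised there will be equal distribution of intervention and control participants". No stratification factor and no variation in block size is described.

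The same section says it is "not possible to blind staff to the allocation" of HCS, although the women themselves are not told what the intervention entails. Study design agrees: after describing the vitamin D part as double blind, it adds "However, the same is not possible for the behaviour change intervention".

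Under Recruitment at 8–12 weeks, "Research nurses approach women who are attending the Princess Anne Hospital for their nuchal translucency or dating scan"; the nurses then check eligibility and take consent. The Healthy Conversation Skills support section describes six part-time research nurses, three for each HCS group. Study setting names a single hospital. Trial status reads "The SPRING trial is ongoing".

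**The concern.** With a fixed, known block size, past allocations reveal future ones. Once two women in a block have gone to the same arm, the next two must go to the other, and the fourth place is always determined. Keeping the list with an impartial data manager conceals the list itself. It does not stop anyone who knows the past allocations from working out the next one, and the block size is now published while the trial is running.

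A recruiter who can foresee the arm could, knowingly or not, time an approach or press the invitation differently, for instance with a woman who seems motivated. The primary outcome for HCS is diet quality from a food frequency questionnaire. It is self-reported and plausibly linked to motivation, so such selection would bias the HCS comparison. A larger sample would not remove that bias. The planned regression adjusts for differences identified at baseline and so cannot correct for motivation that was not measured.

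**Working it through.** **Inputs.** From Randomisation: block size 4, two per arm. From Sample size and power calculation: 150 women per arm needed, 20% drop-out, 188 per arm to be recruited, four arms, target difference 0.25 SD, alpha 0.025. The article gives no figure for predictability.

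**The plan's own figure.** 150 / (1 − 0.20) = 187.5, rounded up to 188, as stated. Total to be randomised: 4 × 188 = 752.

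**Allocations that are certain, fixed blocks of 4.** There are 6 equally likely orders of two 0s and two 1s. The chance that the next allocation is already determined is:
- place 1: 0
- place 2: 0
- place 3: 1/3 (the first two are alike in 2 of 6 orders)
- place 4: 1

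Sum = 4/3 per block of 4, so the share is (4/3)/4 = 1/3. Over 752 women: 752/3 = 250.7, about 251.

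**Best guess, fixed blocks of 4.** Always guess the arm with more places left, and toss a coin when level. The chance of being right by place is 1/2, 2/3, 2/3 and 1. Sum = 2.833; 2.833/4 = 17/24 = 70.8%. Simple randomisation gives 50%.

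**Alternatives.**

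| Scheme | Certain | Best guess right |
|---|---|---|
| Fixed 4 | 33.3% | 70.8% |
| Fixed 6 | 25.0% | 68.3% |
| Fixed 8 | 20.0% | 66.6% |
| Random 4/6, each block's size undisclosed | about 5% | about 69% |
| Random 4/6/8, each block's size undisclosed | about 2% | about 68% |

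The fixed-block rows are exact enumerations. The random-block rows come from simulating lists of 752, with an observer who sees every past allocation and knows which sizes are possible but not which is in use. As a check on the last figure, guessing the under-represented arm in equally frequent blocks of 4, 6 and 8 gives (2.833 + 4.100 + 5.329)/18 = 0.681.

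**What it could do to the diet result (illustration on an assumed effect).** Suppose women steered into the certain HCS places score 0.1 to 0.3 SD higher than they otherwise would. One third of HCS places are certain, so the shift in the HCS mean is 0.1/3 = 0.03 SD to 0.3/3 = 0.10 SD. That is 13% to 40% of the 0.25 SD target. With 300 per group the standard error is √(2/300) = 0.082 SD, and at two-sided alpha 0.025 the false-positive rate would rise from 2.5% to between about 3.7% and 15%. Nothing in the article supports a particular value in this range.

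**The case against.** The strongest reply is that prediction needs conditions the article does not state. Someone must know all past allocations, in randomisation order, across both nurse groups, and know where each block starts. The article describes two groups of three part-time nurses, each in contact with one arm. It does not say that anyone sees the pooled sequence, that the recruiting nurses are these same six, or that there is one unstratified list. A reader might infer that the nurses do know a third of allocations in advance. The text does not support that: one third is an upper limit. Under stratification the share would still be one third within each stratum, but it would be harder to track.

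Timing matters too. Consent is taken around the 8–12 week scan, and the first arm-specific contact described is at about 14 weeks. If nurses learned the arm only then (an assumption), the lag would be 2 to 6 weeks. At 5–8 recruits per week, that leaves 10 to 48 women, or 2.5 to 12 blocks, between consent and visible allocation, so a recruiter would have no current block to read. If the arm is revealed at consent, prediction is easy. The article does not settle which applies.

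There are also partial safeguards. Women are approached at scheduled scans, and every booked woman is sent the leaflet, which limits the scope for steering. Diet and self-efficacy are recorded at about 14 weeks, so measured differences can be adjusted for.

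These points make the risk conditional and lower its likely size. They do not remove it. The fixed block of 4 and the unblinded staff are stated outright, and neither the data manager's impartiality nor adjustment for measured baseline factors prevents selection on a foreseen arm.

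**Conclusion.** The point stands as a conditional risk and a cheap improvement. If recruiting staff can follow past HCS allocations in order and in time, up to one third (about 251 of 752) are certain in advance and a best guess is right 70.8% of the time. If they cannot, the figure is lower, possibly negligible.

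A reader might go further and conclude that the HCS comparison is already biased, or that allocation is released before consent. The article supports neither: it gives no evidence of steering, and nothing in it places allocation ahead of consent. Vitamin D allocation is pre-randomised by the manufacturer and blinded to women and research team, so that comparison is not touched. Sample size and power are unchanged.

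**What to change.** For the allocations that remain, the data manager should replace the list with one using randomly varying block sizes, for example 4, 6 and 8, not disclosed to recruiting staff. The report should state how many women were randomised under fixed blocks of 4, so that readers can judge the exposure. The article does not say how many allocations remain; if none do, only the reporting step applies.

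The gain should not be oversold. Certain allocations fall from 33% to about 2%, but best-guess success falls only from 71% to about 68%, because guessing the under-represented arm needs no knowledge of block size. The change mainly removes certainty. Releasing each allocation only after consent and eligibility are recorded is good practice, but it does not itself prevent prediction from past allocations.

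The cost is a new list, a short amendment and a possible end-of-list imbalance of a few women between HCS and usual care.

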### Early pregnancy

At around 14 weeks gestation women attend the research clinic at Princess Anne Hospital. The timing of this appointment can be later if they are not recruited by 14 weeks. During the appointment, an interviewer-led questionnaire is administered to gather information on parity, baseline demographic features, diet, smoking, alcohol intake, exercise, sunlight exposure, general health, medication, psychological health and wellbeing, self-efficacy and food involvement. Diet is assessed using a 20-item food frequency questionnaire (FFQ) which was developed from a larger FFQ [23]. Data from the FFQ are used to produce a standardised score (with mean 0 and standard deviation 1.0). This score has been named the ‘prudent diet score’. The 20-item FFQ gives closely comparable scores to the full FFQ and can be used in settings where administration of a longer FFQ is not feasible.

For women in the Healthy Conversation Skills intervention group, this appointment also presents an opportunity for the first Healthy Conversation with a trained research nurse. Women are asked about their lifestyle and health behaviours and what they would like to do to ensure they have healthy pregnancies and healthy babies, and to set some goals for achieving this. Details of the conversations and goals are recorded in a Case Report Form and revisited at future appointments.

Women’s height, weight, skinfold thickness (triceps, biceps, subscapular and suprailiac) and grip strength are measured. Venous blood samples are taken and stored with the aim of measuring biomarkers of quality of diet, including beta carotene and vitamin D. With participants’ consent, blood pellets are stored to allow future DNA analysis.

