### 18–21 weeks gestation

Women attend at 18–21 weeks for a National Health Service (NHS) fetal anomaly scan and an additional high-resolution 3D ultrasound scan to obtain detailed measurements of their pregnancies. These scans are performed by the SPRING study sonographer. If any abnormalities are identified, women are referred to their local fetal medicine department for further management and might be excluded from this trial if the diagnosis would make it difficult for them to continue either with the IMP or the study procedures. The findings of any abnormal scans will be recorded as adverse events and thus might inform potential new hypotheses regarding the action of vitamin D in pregnancy. A pill count is performed to assess compliance with the study.

During the 18–21 weeks visit, and after the scan, the intervention research nurses hold a second Healthy Conversation with women in the Healthy Conversation Skills intervention groups to discuss their pregnancies, explore progress towards any goals they set at the 14 week visit and to set new ones if need be. Details of conversations are recorded on the Case Report Form. This forms part of the implementation component of process evaluation. Control research nurses give control group women an information sheet and confirm the timing of the 26 week phone call.

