### Ethical considerations

Information sheets are given to participants outlining the procedures that they will undergo, and plain English is used to facilitate participants’ understanding of the study. Participants also have opportunities, at each follow-up appointment, to discuss any concerns with study staff. The infant DXA assessments are associated with a low dose of radiation exposure, roughly equivalent to 2 days of background radiation in Cornwall (UK) and 7 days in other parts of the UK including Southampton. The dose of vitamin D supplementation has been chosen to bring women just into the normal range (>50 nmol/l circulating 25-hydroxy vitamin D), to avoid elevating to supranormal levels. This approach is consistent with that taken in the MAVIDOS trial of vitamin D supplementation during pregnancy [10]. Previous observational studies in Southampton have suggested low risk of adverse effects from vitamin D supplementation: data from the Princess Anne Cohort study showed a small excess of atopic asthma in children born to mothers with the highest levels of vitamin D in pregnancy [28]. However, numbers of children affected were lower than expected from general population prevalence, and the confidence intervals around the association were wide. No associations between atopy in infancy and high levels of maternal vitamin D have been shown in the Southampton Women’s Survey, and other studies have suggested neutral or negative associations [29–31].

Blood and tissue samples will be processed for storage on the day of collection and will be stored in freezers in the MRC Lifecourse Epidemiology Unit, Southampton General Hospital. They will be stored until all analyses are completed. [name], Director of the Unit and chief investigator for the SPRING trial, will have custodial responsibility, and the samples will be stored in compliance with Human Tissue Authority (HTA) regulations.

There is a potential risk of distress with any interview. Staff will be trained in interviewing techniques and will terminate an interview in the rare event that questions cause participants distress. If a participant should become distressed, she will be reminded of the helpline number and will be referred to support services, a list of which will be available in the research clinic.

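### Not telling women what Healthy Conversation Skills entails does not blind them to receiving it, and the main outcome for that comparison is self-reported diet

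*Protocol article*

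**What the plan says.** The protocol article describes masking of the HCS factor in two places.

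- **Study design.** Women and nurses are "blind to the vitamin D intervention, so this part of the trial is double blind". The next sentence reads: "However, the same is not possible for the behaviour change intervention".
- **Randomisation.** It is "not possible to blind staff to the allocation" of HCS, but "the women themselves will not be told what the intervention entails and so will be blind to the intervention they are receiving".

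The visit sections describe what each woman experiences.

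- **HCS arm.** In early pregnancy women are asked "what they would like to do to ensure they have healthy pregnancies and healthy babies, and to set some goals for achieving this". At 18–21 weeks the nurses "explore progress towards any goals they set at the 14 week visit and to set new ones if need be". Progress is taken up again by telephone at 26 weeks and in person at 34 weeks.
- **Control arm.** At 18–21 weeks, "Control research nurses give control group women an information sheet and confirm the timing of the 26 week phone call". The 26-week call checks personal details and confirms the next appointment. The Healthy Conversation Skills support section says that control nurses have no behaviour change training and do not help women set goals.

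The same section says that both arms have the same number of contacts. Diet quality at 34 weeks, a primary outcome, comes from a 20-item food frequency questionnaire (FFQ).

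**The concern.** A woman can be kept from knowing the name, content or purpose of an intervention and still know that she is receiving it. The Randomisation section treats the first as if it secured the second. For a capsule with a matched placebo this would be sound, because the two experiences are alike. For a series of goal-setting conversations it is not, because the conversations are the intervention and she takes part in them.

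This matters because of how the outcomes are measured. Staff are acknowledged to be unblinded, so blinding of the women is the only masking claimed for the HCS comparison. Where the outcome is the woman's own account of her diet or confidence, that masking is what would protect against women in one arm reporting more favourably than those in the other. A reader who accepts the sentence as written may take a difference in FFQ score as a change in diet, without considering a change in reporting.

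**Working it through.** **1. Contacts side by side, up to the primary diet outcome**

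| Time | HCS arm | Control arm |
|---|---|---|
| About 14 weeks | First conversation, goals set and recorded | Questionnaire and measurements |
| 18–21 weeks | Second conversation, goals reviewed or reset | Information sheet, call time confirmed |
| 26 weeks (telephone) | Conversation on progress towards goals | Details checked, appointment confirmed |
| 34 weeks | Conversation to monitor goals; questionnaire and blood | Nurse contact, standard care; questionnaire and blood |

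The number of contacts is matched and the content is not. Up to three goal contacts precede the 34-week visit in the HCS arm and none in the control arm. The article does not say whether the fourth conversation comes before or after the 34-week questionnaire.

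**2. Outcomes that depend on the woman's report**

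- Primary: FFQ diet score at 34 weeks (one of two).
- Secondary: self-efficacy at 34 weeks, diet one month after birth, and breastfeeding at one month (three of the five entries under Secondary outcomes). Breastfeeding as a yes/no answer is probably less open to a reporting shift than a diet score.
- Plasma 25(OH) vitamin D, weight gain and neonatal DXA measures are not self-reports.
- The one-month questionnaires are given at a home visit by an intervention or control nurse according to HCS allocation.

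**3. The plan's own power figure**

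Inputs from Sample size and power calculation: 300 per group in each comparison, a difference of 0.25 SD, alpha 0.025. Two-sided testing is assumed, since the article does not state it.

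- Standard error in SD units: √(2/300) = 0.0816.
- Critical value: 2.241.
- Power = 1 − Φ(2.241 − 0.25/0.0816) + Φ(−2.241 − 0.25/0.0816) = 79.4%.

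This reproduces the stated 80%. The recruitment target also reproduces: 150/0.80 = 187.5, so 188 per arm. No stated figure is in dispute.

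**4. Illustration of sensitivity to a reporting shift**

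The documents give no estimate of differential reporting, so the shift b is an assumption. With no true effect on diet, the probability of a significant result is 1 − Φ(2.241 − b/0.0816) + Φ(−2.241 − b/0.0816).

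| Assumed shift b (SD) | b as share of 0.25 SD | Probability of a significant result |
|---|---|---|
| 0 | 0% | 2.5% |
| 0.05 | 20% | 5.4% |
| 0.10 | 40% | 15.5% |
| 0.15 | 60% | 34.3% |
| 0.20 | 80% | 58.2% |

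The table shows only that a comparison powered for 0.25 SD is sensitive to modest shifts. It is not evidence that such a shift will occur.

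**The case against.** The strongest reply is that the two sections form a coherent single-blind description. In Study design, the sentence before the disputed one is about women and nurses both being blind, so what is not possible for HCS may simply be double blinding. Randomisation then says which half fails. This stands. A reader might infer that Study design declares the women unblinded and so flatly contradicts Randomisation, but it never says that. It also never says that they are blind to HCS, so it lends the claim no support.

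The second reply is that real masking features exist. Contacts are equal in number, each arm has its own nurses, and a woman sees only her own visits. She may have nothing against which to recognise a conversational style as experimental. Goals are her own choice and need not concern diet. This stands in part. It rules out the stronger reading that there is no masking at all, since some women may be unaware of the hypothesis or of the other arm's experience. It does not make them unaware that a nurse is helping them set and review goals.

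A reader might also take the Ethical considerations section as proof of disclosure, because it says "Information sheets are given to participants outlining the procedures that they will undergo". That line does not say that the sheets describe HCS, and the sheets are not shown, so nothing rests on it here.

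Finally, the article nowhere uses participant blinding to defend the self-reported outcomes, and it plans dietary biomarkers that do not depend on self-report. Both are true. Misreading is therefore a foreseeable consequence and not something the text commits. The biomarkers offer a partial check, but they are not designated outcomes.

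**Conclusion.** The point holds in a limited form. The Randomisation section claims a property, blindness of the women to HCS, that the described delivery does not provide. Non-disclosure can support a narrower statement: women are not informed of the content or hypothesis. Study design and Randomisation leave different impressions and should be aligned.

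The consequence is confined to the HCS comparison on self-reported outcomes: one primary outcome and three secondary entries, with breastfeeding the least exposed. The vitamin D comparison is untouched, as are the sample size and the planned tests. The size of any bias is unknown. The 5.4% to 58.2% in the working rests on assumed shifts of 0.05 to 0.20 SD, 300 women per group and two-sided testing. The conclusion on wording depends on none of these, only on the visit content that the article describes.

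**What to change.** 1. **Randomisation and Study design.** Use one statement in both: for HCS, staff are unblinded; women are not informed of the content or hypothesis but are not blinded to receiving it. Keep the information that content is not disclosed, since it is true and useful.
2. **Interpretation.** State that HCS conclusions on the 34-week FFQ score, one-month diet, self-efficacy and, to a lesser degree, breastfeeding are open to differential reporting.
3. **Corroboration.** Say that the FFQ result will be read alongside beta carotene and vitamin C, already measured at 34 weeks. They are supporting evidence and do not replace the primary outcome.

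An allocation-guess question at one month is not needed. It would come after the 34-week primary outcome and so could not show what women believed when they reported their diet.

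The cost is a few sentences and no new data collection. The downside is that the stated level of masking becomes less favourable.
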